## Abstract

**Background:**

Team-based care has been identified as a key component in transforming primary care. An important factor in implementing team-based care is the requirement for teams to have daily huddles. During huddles, the care team, comprising physicians, nurses, and administrative staff, come together to discuss their daily schedules, track problems, and develop countermeasures to fix these problems. However, the impact of these huddles on staff burnout over time and patient outcomes are not clear. Further, there are challenges to implementing huddles in fast-paced primary care clinics. We will test whether the impact of a behavioral intervention of leadership training and problem-solving during the daily huddling process will result in higher consistent huddling in the intervention arm and result in higher team morale, reduced burnout, and improved patient outcomes.

**Methods/design:**

We will conduct a care-team-level cluster randomized trial within primary care practices in two Midwestern states. The intervention will comprise a 1-day training retreat for leaders of primary care teams, biweekly sessions between huddle optimization coaches and members of the primary care teams, as well as coaching site visits at 30 and 100 days post intervention. This behavioral intervention will be compared to standard care, in which care teams have huddles without any support or training. Surveys of primary care team members will be administered at baseline (prior to training), 100 days (for the intervention arm only), and 180 days to assess team dynamics. The primary outcome of this trial will be team morale. Secondary outcomes will assess the impact of this intervention on clinician burnout, patient satisfaction, and quality of care.

**Discussion:**

This trial will provide evidence on the impact of a behavioral intervention to implement huddles as a key component of team-based care models. Knowledge gained from this trial will be critical to broader deployment and successful implementation of team-based care models.

**Trial registration:**

Clinicaltrials.gov, NCT03062670. Registered on 23 February 2017.

**Electronic supplementary material:**

The online version of this article (10.1186/s13063-018-2847-5) contains supplementary material, which is available to authorized users.

## Background

The Centers for Medicare and Medicaid Services (CMS) has made population health management a key priority as part of its efforts to transform primary care delivery [1]. In 2016, CMS announced $157 million in funding to reform the delivery of primary care to improve both quality and affordability. Research shows that the current approach to delivering primary care using a provider-centric approach is ineffective and may not allow health systems to pursue simultaneously the triple goals of better population health, better patient experiences, and lower per capita costs [2]. There is a need to innovate the primary care delivery model and transition it to a team-based model from a provider-centered care delivery approach. Team-based care has been identified as a key element in transforming primary care [3]. Although theoretical arguments exist on the importance of team-based care in transforming primary care, there is lack of empirical evidence on how team-based care models affect primary care outcomes [4]. With this lack of evidence, the adoption of this model into routine primary care practices has been slow [3]. Making the shift from provider-centric to team-based care has produced high-performing teams when training is one of the components of the implementation [5]. Team training has been found to be useful for improving teamwork, performance, and cognitive and affective outcomes [6]. Team-based care has been endorsed by the Agency for Healthcare Research and Quality (AHRQ) and it now provides online training for implementing team-based care within health-care settings [7]. Within primary care settings, adopting a team-based approach can enhance communication and improve efficiency, particularly with the use of daily huddles.

AHRQ recommends that teams should huddle every morning for at least 10 min [7]. During huddles, the care team, comprising physicians, nurses, and administrative staff, come together to discuss their daily schedules, track problems, and develop countermeasures to fix these problems [8]. Bringing everyone together more frequently has the potential to minimize hierarchical barriers during the delivery of care [9]. Huddles have also been shown to be associated with higher satisfaction of front-line staff and improved communication among the care team [10].

However, many challenges to implementing huddles are also noted in the literature. In a study of six Veterans Health Administration primary care practices that involved over 400 care team members, Rodriguez et al. found that facilitating and encouraging leadership are some of the critical facilitators to daily huddling [11]. Training the physicians to be effective leaders during a huddle can help sustain the practice of huddles [12].

There is very limited evidence on the effectiveness of huddles in enhancing physician engagement in team-based care and problem-solving in outpatient care models. While a few studies argue for the importance of daily problem-solving, these studies are conceptual or based on limited empirical evidence. The gap between the conceptual evidence and successful real-world implementation is limiting our understanding of the impact and the adoption into practice [6, 13].

### Objectives

Through this research we intend to evaluate whether a behavioral intervention of leadership training and problem-solving during the daily huddle will result in better team morale, reduced burnout, and improved patient satisfaction and outcomes over the standard implementation of huddles. Our hypothesis is that the proposed intervention will lead to improved outcomes in a primary care setting.

## Methods/design

This is a multicenter parallel cluster randomized trial in which we test the superiority of huddle optimization training versus standard practice in huddles. Assignment to arms was in a 1–1 ratio. Institutional Review Board (IRB) approval has been obtained from the coordinating center, the Mayo Clinic (approval 16–010146). The trial is registered at clinicaltrials.gov (registration number NCT03062670, registration date 23 February 2017). Our protocol adheres to the SPIRIT recommendations (see Additional file 1) [14].

Primary care clinics in the Midwest United States that are within the Mayo Clinic Health System were eligible for participation if they were certified by the health system as providing team-based care and implementing daily huddles. Care teams in primary care internal medicine, family medicine, or pediatrics were eligible. Care teams seeking enrollment were required to commit to team-based care and implement daily huddles. Within each practice site, care teams were asked to appoint an administrator, a lead physician, and a lead nurse who would attend the huddle optimization training in the event their team was randomized to the intervention arm. All members of the care team who attend huddles were eligible for inclusion and were asked to complete the surveys. Each member has the option to opt out of the surveys.

### Intervention

The intervention comprised a full-day retreat on leadership development, team-based care development, and problem-solving with a focus on huddles as the key strategy. The training at the retreat was provided by experts from the Leadership and Organizational Development Program at Mayo Clinic. Each care team was represented by a physician, a nurse and a clinic administrator.

The retreat consisted of the following learning objectives:Leadership development focusing on physician engagement and teamworkEffective huddling as a leadership practiceProblem-solving focusing on huddles and visual management

Upon completion of the retreat, the research team supported the initiation of daily huddles in the teams randomized to the intervention arm. Other care providers, including pharmacists, receptionists, social workers, and behavioral interventionists, were invited to join the huddles. Each of the intervention teams was assigned to one of the 6 coaches, who provided help and resources during the study period. Biweekly calls, when possible, were established between the coaches and a lead within each care team. There were also coaching visits (at 30 and 100 days) to the individual research sites upon the implementation of these huddles. The content of the coaching was standardized across the treatment sites and primarily involved the lessons learned during the retreat. Specifically, the coaching visits had the following objectives:30-day visit (first interaction): Sustaining the huddling experience100-day visit (second interaction): Effectiveness of problem-solving in huddles and innovation in team-based care

During these visits, there was time for additional interactions with the huddling members and to assess the huddles.

### Standard care

Current standard care varied among the teams. While the huddles were to happen daily, the actual implementation depended on the team. Teams not randomized to the intervention were provided with self-directed training materials related to implementing team-based care, which included an article on the use of huddles developed by Rodriquez et al. [11]. Each team was expected to use these materials to form and conduct huddles per their understanding and their unique needs.

### Outcomes

The primary outcome for the trial is a previously tested and validated team measurement score that consists of 31 questions, asking the respondent to answer “agree” or “disagree” on a four point scale that is converted to a 100 point score per methods referenced in Stock et al. [15]. The team measurement score focuses on four elements of team behavior: communication, roles and goals, cohesion, and team primacy. Responses from each team member will be used to generate an overall score for the team.

Secondary aims include patient satisfaction assessed through Press Ganey ® Medical Practice surveys. These surveys are implemented routinely within the health-care system. After a patient has had an appointment, if they are randomly selected, the survey is sent to them within 30 days for completion. A random sample of each team’s assigned patients that had a recent appointment were surveyed by Press Ganey® every quarter and reported at the site, care team, and provider levels. Patients’ responses are de-identified so that we know who provided the care but not to whom. We receive the percentage of patients who rated their provider with a top score for a given quarter. We monitor the quality outcomes in chronic disease management and prevention to ensure safety and an adequate quality of care are provided in both the control and intervention arms. Quality metrics at the care team level are assessed monthly for diabetes, depression, asthma, hypertension, and vascular issues. The metrics are calculated as the number of patients who met the quality criteria divided by the number of patients who are assigned to the care team who qualify for the assessment. The criteria for each metric are set by Minnesota Community Measures [16].

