### Sample size

Assuming 10 clusters per arm with an intra-cluster correlation of 0.05, with a minimum of three participants per cluster, we would be powered at 90% to detect a 1 standard deviation difference between continuous outcomes. If the cluster size is 10 individuals, then we would be powered at 80% to detect a half standard deviation difference between two continuous outcomes. All calculations are based on a two-sided test with an alpha of 0.05. To ensure there was adequate support for the retreat and that the coaches can support the teams, a maximum of 15 care teams can be randomized into the intervention arm.

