### Statistical methods

All teams will be analyzed in the arm to which they were assigned using techniques appropriate for pragmatic cluster randomized trials. Baseline characteristics will be summarized at the site and care team levels within each trial arm, to provide counts and frequencies for categorical variables and means with standard deviations and ranges for continuous variables. We will test the null hypothesis of no difference between arms in baseline characteristics using *t*-tests and chi-square tests adjusted for clustering by care team.

To account for the effects of care team clustering, we will use hierarchical generalized linear models with random main effects specified at the care team level. Such models are appropriate for analyzing cluster randomized trials and will allow us to account for any imbalances in care team characteristics across study arms. For measures collected from the team members, the outcome of interest will be the 6-month post-baseline responses, adjusting for baseline responses. If there are differences in baseline characteristics between the two study groups, these will be accounted for using hierarchical generalized logistic or linear regression models that include an indicator for study arm.

For outcomes collected at the care team level (patient satisfaction and quality measurements), the percentage of patients who gave the top score for satisfaction and the percentage of patients who met the quality criteria will be compared between arms without accounting for clustering effects, as the data are not available at the individual level.

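### The primary outcome is worded as one score per team but modelled as member responses, and the model clusters by care team although groups of teams were randomised

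*Protocol article*

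**What the plan says.** **Outcome.** The Outcomes section of the protocol article describes a 31-item instrument completed by individuals, "asking the respondent to answer “agree” or “disagree” on a four point scale that is converted to a 100 point score". The description of the primary outcome then ends: "Responses from each team member will be used to generate an overall score for the team".

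**Model.** Under Statistical methods, "we will use hierarchical generalized linear models with random main effects specified at the care team level". The same section states: "For measures collected from the team members, the outcome of interest will be the 6-month post-baseline responses, adjusting for baseline responses". A separate paragraph covers care-team-level outcomes and opens "For outcomes collected at the care team level (patient satisfaction and quality measurements". The team measurement score is not in that list.

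**Unit randomised.** Allocation says that what was randomised was a team or a group of teams. Because staff could work across teams and sites, randomising single care teams was ruled out, and the statistician grouped teams by staff overlap so that each randomised unit was distinct. Trial status gives the counts: 30 care teams in 23 units and, after withdrawal, 11 units (13 care teams) in the intervention arm and 11 units (16 care teams) in usual care.

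**The concern.** There are two related problems with the primary analysis.

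**Level of the outcome.** Taken literally, Outcomes yields one number per team at 6 months, while Statistical methods models one number per respondent. These are different analyses. A team-level score gives each team equal weight unless weights are specified. A member-level model weights teams by how many members respond. Adjusting a member's response for that member's own baseline needs the same person at both surveys, whereas a team score can use whoever answered each time. The Discussion itself expects staff turnover.

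**Level of the random effect.** A random effect for care team treats teams as independent. The Allocation section says that they are not: teams were joined into units because they share staff. If responses are correlated across teams within a unit, a care-team random effect counts more independent clusters than were randomised. The standard error is then too small and the test of the primary outcome is anti-conservative.

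**Working it through.** **1. Does the model fit a one-score-per-team outcome?**
Let Y_j be the single 6-month score of team j, x_j the arm and b_j the baseline score. The stated model would be Y_j = α + βx_j + γb_j + u_j + e_j, with u_j the care-team effect and e_j the residual. With one observation per j, only var(u_j) + var(e_j) can be estimated, not the two parts. The random effect is therefore not identifiable. With several respondents per team it is, so the model fits only the member-level reading.

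**2. Does the stated power depend on that choice?**
Inputs from Sample size: 10 clusters per arm, ICC 0.05, two-sided α 0.05. The first scenario reads "with a minimum of three participants per cluster, we would be powered at 90% to detect a 1 standard deviation difference". The second is 10 individuals per cluster, 0.5 SD, 80% power.

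Take the team score to be the mean of m responses (the article does not say how responses are combined) and SD to be the SD of individuals:

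- SD of a team mean = √(0.05 + 0.95/m).
- m = 10: √0.145 = 0.381. Noncentrality = 0.5 / (0.381 × √(2/10)) = 2.94. Power on 18 df = 79.3% (simulated 79.6%).
- m = 3: √0.3667 = 0.606. Noncentrality = 1 / (0.606 × √(2/10)) = 3.69. Power on 18 df = 93.7% (simulated 93.5%).

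The usual design-effect calculation, 1 + (m − 1) × 0.05, with a normal approximation gives 83.6% and 95.8%. With equal team sizes, the variance of the arm difference is the same for team means as for member responses. So the stated 80% reproduces with one mean score per team, and the stated 90% is conservative.

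**3. What does clustering by care team cost?**
Inputs from Trial status: 13 teams in 11 units and 16 teams in 11 units. Assumptions:

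- m respondents in every team.
- ICC 0.05 lying wholly at unit level.
- Teams spread as evenly as possible over units: 9 units of one team and 2 of two in the intervention arm; 6 of one and 5 of two in usual care.

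With T teams in an arm and t_u teams in unit u, in units of the individual variance:

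- True variance of an arm mean = 0.05 × Σt_u² / T² + 0.95 / (T·m).
- Variance under care-team clustering = 0.05 / T + 0.95 / (T·m).

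Σt_u² = 9 × 1 + 2 × 4 = 17 (intervention) and 6 × 1 + 5 × 4 = 26 (usual care).

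| | m = 10 true | m = 10 care team | m = 3 true | m = 3 care team |
|---|---|---|---|---|
| Intervention, T = 13 | 0.01234 | 0.01115 | 0.02939 | 0.02821 |
| Usual care, T = 16 | 0.01102 | 0.00906 | 0.02487 | 0.02292 |
| Sum | 0.02335 | 0.02022 | 0.05426 | 0.05112 |

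- m = 10: ratio of standard errors = √(0.02022 / 0.02335) = 0.930, about 7% too small. Type I error = 2 × [1 − Φ(1.96 × 0.930)] = 6.8%.
- m = 3: ratio = √(0.05112 / 0.05426) = 0.971. Type I error = 2 × [1 − Φ(1.96 × 0.971)] = 5.7%.

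These figures use the normal distribution, so they isolate the error in the standard error.

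**The case against.** The best defence is that Statistical methods already settles the unit of analysis. It sorts outcomes into those collected from team members and those collected at care-team level, and the team measurement score, being staff survey data, falls in the first class. The instrument is scored per respondent, and the sentence about an overall team score may describe only a summary. Much of this stands, and it is why the member-level reading is the one to confirm. But that sentence sits inside the definition of the primary outcome and nothing labels it as a summary, so the two sections still have to be reconciled. The defence also leaves the level of the random effect untouched.

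On that second point, it can be said that the correlation may lie mostly within care teams, in which case clustering by care team loses little. That is possible, and the article gives no split of the ICC. But the Allocation section's own reason for forming units was shared staff, so independence between teams of one unit is hard to assume.

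A reader might go further and infer that the stated 80% and 90% power do not fit a team-level endpoint. The document does not support this. Power falls well short only if SD is taken to mean the SD of team scores. The Sample size section works with an ICC and individuals per cluster, which would have no role if it meant that. On the individual SD, a test on team means gives 79.3% and 93.7%.

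A reader might also object that the Abstract calls the outcome team morale. The Outcomes section identifies the instrument and its four domains, so this is a matter of naming and does not affect the analysis.

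**Conclusion.** The point holds in two parts. First, Outcomes and Statistical methods disagree on whether the primary outcome is a team score or a member response, and the stated model can be fitted only to the latter. Second, the random effect is placed at care-team level although the randomised units are groups of teams.

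The second part has a size. Under the illustrative assumptions the standard error is about 7% too small with 10 respondents per team, and the type I error is near 6.8%. With 3 respondents per team it is about 5.7%. These figures rest on equal numbers of respondents per team, on the whole ICC of 0.05 lying at unit level, and on the most even spread of teams over units. A less even spread raises Σt_u² and so the error; correlation confined within care teams lowers it. Trial status also mentions two further care teams that withdrew. Since 13 + 16 = 29 = 30 − 1, they appear still to be counted, and I have used the counts as printed.

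The sample size statement is sound on this point and needs no change.

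**What to change.** - In Outcomes, define the primary endpoint as each respondent's 0-100 team measurement score at 6 months, and state that the overall team score is a descriptive summary.
- In Statistical methods, analyse that score at individual level, adjusted for baseline, with a random intercept for the randomisation unit. Care team may be nested within unit as a further random effect.

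The first change is wording only. The second alters the specification of the primary model, but it needs no new data: the units were formed before randomisation and are known to the statistician. The 11 units per arm still meet the 10 clusters per arm assumed in Sample size. Trial status reports data collection as ongoing, so both changes can be fixed before the analysis.

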### Participant timeline

Participation in the study for the care teams ended when the last survey was administered at 6 months post the start of the intervention (Fig. 1). Further data will be collected from medical records at the care team level up to 12 months after the end of the intervention, but no contact with the participants will be needed.

**Fig. 1 Fig1:**
[figure not shown]
Study flow diagram

### Sample size

Assuming 10 clusters per arm with an intra-cluster correlation of 0.05, with a minimum of three participants per cluster, we would be powered at 90% to detect a 1 standard deviation difference between continuous outcomes. If the cluster size is 10 individuals, then we would be powered at 80% to detect a half standard deviation difference between two continuous outcomes. All calculations are based on a two-sided test with an alpha of 0.05. To ensure there was adequate support for the retreat and that the coaches can support the teams, a maximum of 15 care teams can be randomized into the intervention arm.

### Recruitment

All sites that meet the eligibility criteria were contacted via email for participation in the trial. All administrators, physicians, and nurses were sent the email asking for a representative of the care team to contact the study team with consent to participate. The email, with text approved by the IRB, was used as the invitation for participation and consent to participate (Additional file 2).

